## Abstract

**Background:**

Negative symptoms and cognitive deficits are two partially-related features of schizophrenia which have a major negative impact on social function and objective quality of life. Standard drug treatments have little impact on either. There is some evidence that anti-inflammatory treatment may have beneficial effects in schizophrenia and major depression. Statins are cholesterol-lowering agents that have been found to be anti-inflammatory agents and are also known to decrease C-reactive protein (CRP). Ondansetron is a serotonin (5-HT3) receptor antagonist widely used to prevent nausea and vomiting in patients receiving chemotherapy for cancer. Small studies have suggested that ondansetron is effective as an adjunct drug in improving the symptoms of schizophrenia.

**Methods/design:**

This is a two center, six-month, double-blind placebo controlled, factorial design study of ondansetron and/or simvastatin added to treatment as usual for patients suffering from schizophrenia, schizoaffective disorder, psychosis not otherwise specified or schizophreniform disorder. This will be a 2 × 2 design, with 54 patients in each cell, giving a total of 216 patients over three years. There will be a screening, a randomization and seven follow-up visits. Full clinical and neurocognitive assessments will be carried out at baseline (randomization), 14 weeks and at 26 weeks, while the positive and negative syndrome scale (PANSS), pill count and side effects checklist will be carried out at every visit. Simvastatin will be started at 20 mg once daily (OD), this will be increased to 40 mg after four weeks. Ondansetron will be administered in an 8 mg dose.

**Discussion:**

Anti-inflammatory treatments have been shown to have some beneficial effects in schizophrenia. Both simvastatin and ondansetron provide some evidence of a reduction in symptoms compared to treatment as usual. The aim of this study is to establish the degree of improvement in negative symptoms with the addition of ondansetron and/or simvastatin to treatment as usual.

**Trail registration:**

ClinicalTrails.gov NCT01602029

## Background

Although dopamine remains the primary neurotransmitter implicated in pathogenesis of schizophrenia, there is growing evidence to support inflammatory processes to be involved as well [1]. A number of studies have reported increased peripheral inflammatory cytokines (interleukin-1 (IL-1), IL-2, IL-6, and tumor necrosis factor alpha) [2] and elevated IL-1 in cerebrospinal fluid (CSF) of patients with schizophrenia [3]. In the brain, cytokines seem to be involved in regulating the action of several neurotransmitters, such as serotonin, noradrenaline, dopamine and glutamate. The interaction of cytokines with dopamine and glutamate seems to be especially relevant to the pathophysiology of schizophrenia [4].

Currently available treatments for schizophrenia are effective in treating positive symptoms, but have little or no impact on primary negative symptoms [5]. Negative symptoms and cognitive deficits are two partially-related features of schizophrenia which have a major negative impact on social function and objective quality of life [6]. Social dysfunction has major economic consequences in both the developed and developing world.

There is evidence that anti-inflammatory treatment may have beneficial effects in schizophrenia. In preliminary clinical trials for treatment of schizophrenia, Cox-2 inhibitors have shown favorable effects [1,7]. In our recent randomized double-blind placebo-controlled clinical trial in Pakistan and Brazil, the addition of minocycline (an antibiotic and anti-inflammatory drug) for one year to treatment as usual (TAU) reduced negative symptoms and improved some cognitive measures [8].

Statins are primarily HMG-CoA reductase inhibitors but are also anti-inflammatory agents. Similar to the Cox-2 inhibitors, they have the potential to improve these symptoms of schizophrenia [9]. The statins are also known to decrease C-reactive protein (CRP), which has been shown in an SMRI-funded study to be elevated in schizophrenia. Fan *et al.*[10] demonstrated in patients with schizophrenia higher levels of CRP (>0.50 mg/dl) to be associated with marked negative symptoms and higher total positive and negative syndrome scale (PANSS) scores.

Ondansetron, a selective 5-hydroxytryptamine-3 antagonist, is used quite commonly as an antiemetic in cancer patients [11]. There are several small trials suggesting that ondansetron, as an adjunct to antipsychotics, is effective in improving negative symptoms and memory in patients suffering from schizophrenia [12-14]. There is also evidence that 5HT3 antagonists have some anti-inflammatory effects through inhibition of TNF-alpha/interlukin-1beta secretions in human monocytes [15].

### Preliminary study

We conducted a small, placebo-controlled, rater-blind 12-week feasibility study adding ondansetron or simvastatin to TAU in 36 patients with chronic schizophrenia (ClinicalTrails.gov NCT00929955). Statins and ondansetron are well tolerated and their side effect profiles well understood. The aim of this study was to examine the tolerability of both compounds and allow estimation of effect sizes to power a larger trial. Both treatments were well tolerated and no serious side effects were reported.

### Aims

We propose to test the prediction that addition of ondansetron and/or simvastatin to TAU for patients with schizophrenia will result in the following outcomes:

•Primary: improvement in negative symptoms

•Secondary:

improvement in positive or other symptoms

improvement in social functioning

improvement in cognitive functions

possible additive effects of ondansetron and simvastatin added to TAU

## Methods/design

### Overview

This is a two center, six-month, double-blind placebo-controlled, factorial design study of ondansetron and/or simvastatin added to treatment as usual for patients suffering from schizophrenia, schizoaffective disorder, psychosis not otherwise specified or schizophreniform disorder. This will be a 2 × 2 factorial design, with 54 patients in each cell, giving a total of 216 patients over three years (Table 1).

**Table 1 T1:** 2 × 2 Factorial design

	**Placebo**	**Simvastatin**	**Total**
Placebo	54	54	108
Ondansetron	54	54	108
Total	108	108	

The advantage of a factorial design is the effective sample size for each drug is 108 for each treatment factor. However, in addition it allows a test of scientifically and clinically interesting possibility that the two drugs have additive or even multiplicative benefits. A possible minor disadvantage is that all participants take two types of pills.

The study will be conducted in Karachi, Pakistan and San Paulo, Brazil. The patients will be recruited both from inpatient and outpatient settings. The patients will be identified and first approached by the treating psychiatrists and the multi-disciplinary teams (MDT). The patients will continue to take treatment as usual during the trial. While the study assessments will be done by the research assistants (RAs), the responsible psychiatrist will remain in charge of the overall treatment. Any changes to dose or types of medications will be recorded on monthly reviews.

After consenting to take part in the study, the clinical symptoms, cognitive, neurological and general level of function of the participants will be assessed. When these measures are completed, the patient will be randomized to one of the four treatment arms. During the course of the study the patient will also have additional support by doctors and RA from the research team and continued support from their mental health care team. If necessary, members of the research team will be available 24 hours a day, 7 days a week.

### Allocation

In this study patients will be allocated to treatment group according to a randomized permuted blocks algorithm, after stratification by center. Allocation will be determined in Manchester by pseudo-random number generation by the trial statistician. The results will be conveyed to the trial pharmacist so that medication can be given to participants without anyone else on the team being aware of the allocation (that is, double blind).

### Power calculation and statistical analysis

Our previous experience with trials in this area [8] and the pilot lead us to expect 20% dropout across all cells. In that case, we will have outcomes on 43 participants within each cell of the design. Assume, for the sake of illustration, that the mean PANSS negative score in the cell without either drug is 20 points after six months. Also assume that the single-drug-only cells (B and C) both have a mean PANSS negative score of 18 points. Finally, after treatment with both drugs (D), mean outcome score is 17 points (that is, a departure from additivity). The within-cell standard deviation is taken to be about five units. Using a two-way analysis of variance with a significance level of 0.05, the trial will have about 45% power to detect departures from additivity of this size. It will have about 80% power to detect differences between the cells with and without ondansetron in the cells without simvastatin (that is, A versus C), and, similarly, the differences with and without simvastatin in the two cells without ondansetron (A versus B). The following is based on the assumption that the two treatment effects are, indeed, additive (no interaction). When testing the effects of ondansetron, for example, the contrast will compare the mean of the 86 participants allocated to receive this drug with the mean of the 86 who were not (C and D versus A and C), and the trial will have over 90% power to detect the overall effects based on this contrast (Table 2).

**Table 2 T2:** Statistical analysis plan

	**Placebo**	**Simvastatin**	**Total**
Placebo	A	B	(A + B)/2
Ondansetron	C	D	(C + D)/2
Total	(A + C)/2	(B + D)/2	

All analyses will be based, as far as possible, on the intention-to-treat principle (with weighting adjustments to allow for differential loss to follow-up – see below). Analysis of the three- and six-month quantitative outcomes will be based on an analysis of covariance (ANCOVA), using relevant baseline score and center membership as covariates. In line with the factorial design, we will initially evaluate the interaction between ondansetron and simvastatin. If this (as expected) is not statistically-significant, we will proceed to estimate the main effects of each of these two drugs separately (that is, in terms of the 2 × 2 design in the table above, by comparison of row means for ondansetron and column means for simvastatin, respectively). If the interaction was found to be statistically-significant the analysis would involve the estimation of all of the parameters of the saturated model. Patterns of missing outcome data will be examined as a function of recorded baseline characteristics and patterns of compliance with the treatment protocol. Adjustments will be made to allow for biases arising from patterns of missing outcome data linked to protocol violations using inverse-probability weighting.

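### The printed power of about 45% for the assumed departure from additivity is about 10% on the protocol's own inputs

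*Protocol article*

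**What the plan says.** All the inputs stand in the protocol article, mostly under Power calculation and statistical analysis. The trial randomises "with 54 patients in each cell, giving a total of 216 patients over three years (Table 1"). Earlier experience and the pilot "lead us to expect 20% dropout across all cells", so that "we will have outcomes on 43 participants within each cell of the design". The assumed six-month PANSS negative means are 20 with neither drug (A) and 18 with either drug alone (B and C); "after treatment with both drugs (D), mean outcome score is 17 points (that is, a departure from additivity"). The within-cell SD is about five. "Using a two-way analysis of variance with a significance level of 0.05", the section concludes that "the trial will have about 45% power to detect departures from additivity of this size". It then gives about 80% power for A versus C and for A versus B, and over 90% for each drug's overall effect.

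Two other places bear on the interaction. The Overview counts it as a merit of the factorial design that "it allows a test of scientifically and clinically interesting possibility that the two drugs have additive or even multiplicative benefits". The Aims list, among the secondary outcomes, "possible additive effects of ondansetron and simvastatin added to TAU".

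**The concern.** An interaction contrast combines four cell means, so its standard error is twice that of a main effect estimated from the same patients. Here the assumed departure (1 point) is also only half of either drug's assumed single-drug effect (2 points). Power of 45% for so small a contrast, at a size where a 2-point comparison of two cells is itself weakly powered, does not look possible.

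What is at stake is how a null interaction is read. The analysis section tests the interaction first, expects it to be non-significant, and then moves to main effects. A reader given 45% would think that a departure of the assumed size is missed 55% of the time. At 10% it is missed about 90% of the time, and the test is barely more likely to reject than under exact additivity (5%).

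**Working it through.** **Inputs, all printed:** A = 20, B = 18, C = 18, D = 17; SD = 5; n = 43 per cell (54 × 0.8 = 43.2); alpha = 0.05. The one-degree-of-freedom interaction F test is two-sided by construction.

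**Attempt to reproduce 45%**

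- Additive prediction for D: 18 + 18 − 20 = 16. Departure: A − B − C + D = 20 − 18 − 18 + 17 = 1 point, in the sub-additive direction.
- Standard error: 5 × √(4/43) = 1.525.
- Standardised effect: 1/1.525 = 0.656.
- Normal approximation: Φ(0.656 − 1.960) = 9.6%.
- Noncentral F with 1 and 168 degrees of freedom: 10.0%. A simulation of 100,000 trials gives 9.9%.

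The printed 45% is not reproduced.

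**Variants that might rescue it**

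| Variant | Power for the 1-point departure |
|---|---|
| No dropout, 54 per cell | 11.3% |
| One-sided 0.05 | 16.1% |
| Two-sided 0.10 | 17.1% |
| SD 4 / SD 6 | 12.9% / 8.4% |
| Main-effect standard error used by mistake | 25.8% |
| Three-degree-of-freedom test of all four cells | 65.3% |
| ANCOVA, assumed baseline correlation 0.5 | 11.7% |
| ANCOVA, assumed baseline correlation 0.7 | 15.0% |
| ANCOVA, assumed baseline correlation 0.9 | 32.2% |

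The article gives no baseline correlation, so the ANCOVA rows are assumptions, with residual SD = 5 × √(1 − r²).

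**What 45% would need:** a departure of about 2.8 points, larger than either drug's assumed effect; or a residual SD of about 1.8 (r about 0.93); or about 337 analysable patients per cell. For 80% power at 43 per cell the departure must be about 4.3 points; for 80% power at 1 point, about 785 per cell are needed.

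**Precision:** the expected 95% confidence interval half-width for the interaction is 1.974 × 1.525 = 3.01 points, three times the assumed departure.

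**Neighbouring figures, same inputs**

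| Contrast | Difference | Standard error | Recomputed | Printed |
|---|---|---|---|---|
| A v C (or A v B) | 2 | 5 × √(2/43) = 1.078 | 45.0% | about 80% |
| A v D | 3 | 1.078 | 78.5% | none |
| Main effect, additive | 2 | 5 × √(2/86) = 0.762 | 74% | over 90% |
| Main effect from the printed means, 19 v 17.5 | 1.5 | 0.762 | 50% | over 90% |

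The 45% printed for the interaction is the value for A versus C, and the 80% printed for A versus C is close to the value for A versus D. That pattern is consistent with figures attached to the wrong contrasts, but the article does not show how they were obtained.

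**The case against.** The best defence is that the article never calls 45% adequate. It offers the means as an illustration, and power below one half already warns that a null result is weak. No sample size is said to rest on this figure; the stated gain of the design is 108 patients per drug for the main effects. All of that stands, and it limits the weight of the point. It does not make a power value correct for the means it is attached to.

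A second defence is covariate adjustment, since the planned analysis is an ANCOVA. With an assumed correlation of about 0.75 (residual SD about 3.3), A versus C reaches 80% and a 2-point main effect exceeds 90%, so those two figures could have arisen that way. The interaction would still have only about 17%. The paragraph also names a two-way analysis of variance and an SD of five. No single SD gives both 45% for the interaction (which needs about 1.8) and 80% for A versus C (which needs about 3.3).

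A reader might go further and infer that the trial cannot study the two drugs together, or that the secondary aim must be rewritten. The documents do not support either step. The interaction test can be run whatever its power, and the Overview sentence claims only that the test is possible. Both drugs against neither (A versus D) has about 79% power on the same inputs. The secondary aim concerns additive effects, and additivity is the null hypothesis of the interaction test, so a wrong power for a departure from it does not undermine the aim.

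Nor is a non-significant interaction empty in every respect. A departure of 4.3 points would be found with 80% power; only departures near the assumed 1 point are out of reach.

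**Conclusion.** Wrong as written. On the printed means, SD, cell size, test and significance level, power for the assumed departure from additivity is about 10%, not about 45%: an overstatement of 35 percentage points. The result does not depend on dropout (11.3% with all 54 per cell), on reading the SD as anywhere from 4 to 6 (12.9% to 8.4%), or on a plausible baseline adjustment (15.0% at an assumed correlation of 0.7).

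The consequence is limited to interpretation. For the assumed 1-point departure, a non-significant result favours additivity by 0.95/0.90, about 1.06 to 1, against 0.95/0.55, about 1.7 to 1, if the printed power were true. Such a result should therefore not be read as support for additivity. The primary outcome, the sample size and the analysis model are unaffected by this figure. That the 45% was taken from A versus C is an inference from a close numerical match, and the error stands without it.

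**What to change.** Replace the interaction figure with a statement to this effect: *about 10% power to detect a 1-point departure from additivity; a departure of about 4.3 points is detectable with 80% power*. Add that the interaction estimate is expected to have a 95% confidence interval half-width of about 3 points, so that readers can judge what a null result rules out.

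In the same pass, recheck the 80% and over-90% figures from the same inputs. If they assume a baseline-adjusted residual SD, state that SD and use it for all three figures.

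The secondary aim can stay as worded. The cost is two or three corrected sentences and less favourable printed figures; no patients, visits or analyses are added.

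### The stated power of about 80% for each single-drug comparison (A versus C, A versus B) is about 45% on the plan's own inputs

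*Protocol article*

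**What the plan says.** All of this is in the protocol article, mainly under *Power calculation and statistical analysis*.

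- **Sample size.** The *Overview* states: "This will be a 2 × 2 factorial design, with 54 patients in each cell, giving a total of 216 patients over three years". Previous experience and the pilot "lead us to expect 20% dropout across all cells", so "we will have outcomes on 43 participants within each cell of the design".
- **Means.** The illustration supposes that "the mean PANSS negative score in the cell without either drug is 20 points after six months". It continues: "Also assume that the single-drug-only cells (B and C) both have a mean PANSS negative score of 18 points". Cell D, with both drugs, is given a mean of 17.
- **Spread and test.** "The within-cell standard deviation is taken to be about five units". The method named is a two-way analysis of variance at the 0.05 level; sidedness is not stated.
- **Claim.** "It will have about 80% power to detect differences between the cells with and without ondansetron in the cells without simvastatin (that is, A versus"; the comparison cell named next is C, and the same claim is made for A versus B.
- **Use of these comparisons.** The interaction is tested first. If it is not significant, main effects are estimated from row and column means. Otherwise: "If the interaction was found to be statistically-significant the analysis would involve the estimation of all of the parameters of the saturated model".

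**The concern.** The 80% claim sits in the same paragraph as all the numbers needed to check it, and a difference of 0.40 SD with 43 per group is well short of 80% power by any usual calculation. It is also a separate claim from the figure of over 90% given for the pooled contrast of 86 against 86, so pooling cannot explain it.

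A versus B and A versus C are the effects of each drug given alone. With A as the reference cell, they are the single-drug parameters of the saturated model that the plan turns to if the interaction is significant. A reader who trusts the 80% would take a non-significant single-drug result as a fairly informative negative on the primary outcome. At the true power it would say little.

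**Working it through.** **Inputs** (all from *Power calculation and statistical analysis*, except the 54 per cell, from the *Overview*)

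- Analysed per cell: 54 × 0.80 = 43.2, stated as 43
- Difference A − C = A − B: 20 − 18 = 2 points
- Within-cell SD: 5, so the standardised difference is 2/5 = 0.40
- Significance level 0.05, taken as two-sided because sidedness is not stated; one-sided is also tried

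**Attempt to reproduce the 80%**

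Standard error of the difference: 5 × √(2/43) = 1.078.

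Noncentrality: 2 / 1.078 = 1.855. This is below the two-sided critical value (1.99 on 84 df, 1.97 on 168 df), so power must be under one half.

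| Variant | Power for A versus C (or A versus B) |
|---|---|
| Two-sided, two-cell error (84 df) | 45.0% |
| Two-sided, pooled ANOVA error (168 df) | 45.4% |
| Two-sided, normal approximation | 45.8% |
| One-sided, 43 per cell | 58% |
| Two-sided, no dropout (54 per cell) | 54% |
| One-sided, no dropout (54 per cell) | 66–67% |

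The last row is the most favourable reading of the printed inputs, and it sets aside the plan's own 20% dropout. It is still about 13 points short.

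**What 80% would take (two-sided, noncentral t, changing one input at a time)**

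- Difference at 43 per cell and SD 5: about 3.06 points
- SD at 43 per cell and 2 points: about 3.27
- Analysed patients per cell at 2 points and SD 5: about 100

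**Could baseline adjustment supply the gain?**

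The planned analysis is ANCOVA with baseline score and centre. If 5 is the raw SD, the residual SD is 5 × √(1 − r²), where r is the baseline-outcome correlation. The protocol gives no r, so a range of 0.3 to 0.7 is assumed here.

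| r (assumed) | Residual SD | Two-sided power, 43 per cell |
|---|---|---|
| 0.3 | 4.77 | 48% |
| 0.5 | 4.33 | 56% |
| 0.7 | 3.57 | 73% |

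Reaching 80% needs a residual SD of 3.27, that is r = √(1 − (3.27/5)²) ≈ 0.76.

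That value does not reconcile the paragraph. The interaction contrast on the printed means is 20 − 18 − 18 + 17 = 1 point, with standard error SD × √(4/43). At a residual SD of 3.27 its power is about 17%, against the 45% printed. Getting 45% for the interaction would need an SD of about 1.8. No single SD gives both printed figures.

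**Possible origin (conjecture).** A versus D, a 3-point difference, has 79% power at 43 per cell. The 45% printed for the interaction is also what A versus C actually has. Figures may have been attached to the wrong contrasts, but nothing in the protocol settles this and the result does not depend on it.

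**The case against.** The arithmetic itself is not open to dispute; the case on the other side concerns its weight.

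- **These are not the primary contrasts.** The plan expects a non-significant interaction and would then use row and column means. On its own scenario the 1-point interaction has about 10% power at SD 5, so the saturated model would seldom be reached. Even then the text speaks of estimation, not of a significance test for each drug, and it nowhere says a null result would be read as no effect. This stands and limits the practical damage. It does not make the printed figure right.
- **The means are illustrative and the SD approximate.** True, but the 80% is claimed from them, and the SD would have to be about 3.3 rather than 5.
- **ANCOVA is planned and sidedness is unstated.** Combining assumptions can pass 80%: one-sided with r = 0.7 gives about 82% at 43 per cell. So 67% is a ceiling only for the printed inputs. But the power text names an analysis of variance with a within-cell SD, and mentions neither a covariate gain nor a one-sided test.
- **Other figures in the paragraph fail too.** From the same inputs the interaction has about 10% power (printed: about 45%), and an additive 2-point main effect at 86 per side has about 74% (printed: over 90%). This stands, and it bears on how the correction is made.

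**Conclusion.** The figure is wrong as written. On the protocol's own inputs the power for A versus C and for A versus B is about 45%, not about 80%: a shortfall of about 35 percentage points. Each comparison would miss the assumed 2-point effect about 55% of the time.

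This rests on a two-sided 0.05 test, 43 analysed per cell, and 5 as the SD that applies to the comparison. A one-sided test gives 58%. Only a correlation or a residual SD that the protocol does not state would bring the figure to 80%. The error concerns a secondary branch of the analysis, but it is a printed power claim contradicted by the numbers beside it.

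**What to change.** Replace the 80% for A versus C and A versus B with about 45% power for a 2-point difference, or say that 80% power holds only for a difference of about 3.1 points. Add that single-cell comparisons will be reported as estimates with confidence intervals, and that a non-significant result is not evidence of no effect.

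If a gain from baseline adjustment was intended, state the residual SD used and its source. The value of about 3.3 is back-calculated from the 80% and is not evidence for itself. State the sidedness of the test as well.

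Recompute the interaction and main-effect figures at the same time. Otherwise the corrected paragraph would print 45% for both the interaction and the single-drug comparisons, and the former would still not follow from the inputs.

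The cost is one corrected sentence, plus the recheck of its neighbours. No patients are added and the design is unchanged; the stated power becomes less favourable.

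### The power of over 90% stated for each drug's main effect does not follow from the printed inputs: it is about 74% for the 2-point effect, and the two companion power figures fail on the same inputs

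*Protocol article*

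**What the plan says.** The Overview describes a 2 × 2 factorial trial "with 54 patients in each cell, giving a total of 216 patients". The section Power calculation and statistical analysis says that earlier experience and the pilot "lead us to expect 20% dropout across all cells", so that "we will have outcomes on 43 participants within each cell of the design".

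For illustration it takes mean PANSS negative scores at six months of 20 with neither drug (cell A), 18 with either drug alone (B and C) and 17 with both (D), and it calls this last value a departure from additivity. On spread it says: "The within-cell standard deviation is taken to be about five units". The method is given as "Using a two-way analysis of variance with a significance level of 0.05".

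Three power figures follow:
- about 45% for the departure from additivity;
- about 80% for each single-drug cell against cell A;
- for the main effect of each drug, now assuming additivity and 86 versus 86 analysed, "the trial will have over 90% power to detect the overall effects based on this contrast".

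The last contrast is labelled "C and D versus A and C". No effect size, SD or baseline correlation specific to this figure is given.

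**The concern.** A main-effect comparison of 86 with 86 at SD 5 has a standard error of about 0.76 points, so a 2-point effect is only about 2.6 standard errors. Power above 90% needs more than 3.2.

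The main effects test the primary aim, improvement in negative symptoms, and this figure supports the sample size of 216. If a drug shows no significant effect, a reader who trusts the figure will think that the trial had less than a 10% chance of missing the assumed effect. On the printed inputs that chance is about 26%. The analysis also begins with the interaction test, so the power stated for that test affects how much weight a non-significant interaction can carry.

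**Working it through.** **Inputs**, all from Power calculation and statistical analysis: 43 analysed per cell (54 × 0.8 = 43.2), hence 86 per level of each factor; SD 5; means A 20, B 18, C 18, D 17; significance level 0.05. Sidedness is not stated, but a 1-df F test in a two-way ANOVA is equivalent to a two-sided t test.

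**Main effect under additivity.** The effect is not restated for this case. The only single-drug effect given is 20 − 18 = 2. Additivity then puts D at 20 − 2 − 2 = 16, and the marginal effect is (20 + 18)/2 − (18 + 16)/2 = 2.
- SE = 5 × √(2/86) = 0.762
- 2/0.762 = 2.62
- Power ≈ Φ(2.62 − 1.96) = 74.6%; noncentral t with 168 df, 74.2%
- Effect detectable with 90% power: (1.960 + 1.282) × 0.762 = 2.47 points
- Analysed patients per level for 90% power at 2 points: about 132, against 86

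The stated figure is not reproduced.

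**Single-drug cell comparison (A versus B, or A versus C).**
- SE = 5 × √(2/43) = 1.078
- 2/1.078 = 1.85
- Power ≈ Φ(1.85 − 1.96) = 46%; noncentral t, 45%

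**Interaction.** The departure is (20 − 18) − (18 − 17) = 1 point.
- SE = 5 × √(4/43) = 1.525
- 1/1.525 = 0.66
- Two-sided power about 10%

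| Comparison | Stated | From printed inputs |
|---|---|---|
| Main effect, 2 points, additive | over 90% | about 74% |
| A versus B or C, 2 points | about 80% | about 45% |
| Interaction, 1 point | about 45% | about 10% |

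**Attempts to recover the stated figures** (normal approximation, printed means unless stated):

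| Variant | Main effect | A versus B or C | Interaction |
|---|---|---|---|
| One-sided 0.05 | 84% | 58% | 16% |
| No dropout (108 per level) | 84% | 55% | 11% |
| One-sided and no dropout | 90% | 67% | 18% |
| Baseline correlation 0.5 (SD 4.33) | 86% | 57% | 12% |
| Baseline correlation 0.6 (SD 4.0) | 91% | 64% | 13% |
| Baseline correlation 0.75 (SD 3.31) | 98% | 80% | 17% |
| Baseline correlation 0.8 (SD 3.0) | 99% | 87% | 19% |
| 3-point single-drug effect, SD 5 | 98% | 79% | 10% (1-point departure kept) |

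The correlation rows use SD = 5√(1 − r²). Power of 90% at 2 points needs an SD of about 4.05, that is r of about 0.6. Some variants recover one or two of the figures; none recovers all three. With the 1-point departure, 45% interaction power needs an SD of about 1.8.

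**Secondary note.** The non-additive illustration implies a marginal effect of 19 − 17.5 = 1.5 points. Then 1.5/0.762 = 1.97, and power is about 50%.

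**The case against.** The strongest reply is that the inputs, not the outputs, may be misprinted. The 80% and the over 90% agree with each other: a ratio of effect to SD that gives 80% at 43 versus 43 gives about 98% at 86 versus 86. A 3-point effect with SD 5, or a 2-point effect with SD about 3.3, fits both. This stands as a possibility. The document cannot settle which number is wrong, and neither variant gives 45% for a 1-point interaction. It shapes the remedy but does not remove the inconsistency.

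A second reply is that the planned analysis is an ANCOVA with baseline score as a covariate. That is true, so 74% is the unadjusted figure and not necessarily the power of the final analysis. But the calculation is declared as a two-way ANOVA, no correlation is stated, and the r of about 0.6 that rescues the main effect leaves the other two figures at 64% and 13%.

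Three stronger readings are not supported:
- *That the stated 90% is really 50%.* The 50% belongs to the non-additive illustration. The figure above 90% is claimed only under additivity, so 74% is the like-for-like comparison.
- *That the primary contrast is misdefined.* The label "C and D versus A and C" puts cell C on both sides, but the same sentence describes the comparison correctly in words, and both Table 2 and the planned comparison of row means define it correctly. It is a clerical slip that changes no calculation.
- *That the Overview's claim is a further error:* "The advantage of a factorial design is the effective sample size for each drug is 108 for each treatment factor". This is the number randomised per level, before dropout.

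**Conclusion.** The point holds: the power paragraph is wrong as written. Under additivity the main-effect power is about 74%, not over 90%, and the companion figures are about 45% and 10%, not about 80% and 45%. All three are overstated, by margins too large for rounding or for an SD of only about five to explain.

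The 74% rests on carrying the 2-point single-drug effect into the additive case, 86 analysed per level, SD 5, a two-sided 0.05 test and no credit for baseline adjustment. The inconsistency itself is certain. Which of the printed numbers is at fault is not, so the paragraph does not by itself show that the trial is too small. It shows that the stated power cannot be relied on until the inputs and outputs agree.

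**What to change.** Reconcile the cell means, the SD and all three power figures together, by one of two routes:

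1. If the printed means and SD are right, restate the powers as about 74% for the main effect (2 points, additive), about 45% for a single-drug cell against cell A, and about 10% for the 1-point interaction. Add that 90% main-effect power corresponds to about 2.5 points. The 50% for the non-additive illustration can be given as a note.
2. If another effect size, SD or baseline correlation was used, state it and recompute all three figures from it. A correlation of about 0.6 is what 90% at 2 points requires.

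Changing only the main-effect sentence would not do: about 80% at 43 versus 43 cannot stand beside 74% at 86 versus 86 for the same 2-point effect. In the same edit, correct the contrast label to C and D versus A and B.

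The cost is one reworded paragraph. No patients, visits or analyses are added. The downside is a less favourable stated power.
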